#### Secondary clinical endpoints

Self-reported at baseline and at 3, 6 and 12 months after end of intervention:Responses to treatment defined as a reduction in PAC-QOL score of at least 0.4 point [58–60]Binary responses to treatment defined as either a 1-point (or greater) reduction in PAC-QOL score [58–60]PAC-QOL: individual domains and total score (as continuous variables)Patient Assessment of Constipation–Symptoms (PAC-SYM) score [61]: individual domains and total score (as continuous variables)A 2-week patient diary (for 2 weeks prior to each assessment) to record bowel frequency and whether each evacuation was ‘spontaneous (no use of laxatives) and/or complete’; journal will also capture concurrent medication, health contacts, time away from normal activities (including work) since the patient’s last visitGeneric quality of life: the EuroQol Health Outcome Measure (EQ-5D-5 L) [62] descriptive system and the EuroQol Visual Analogue Scale (EQ-VAS) [63]NHS resource use: interventions, treatment sequelae and other health resource use related to the care of CCPatient costs related to constipation and the opportunity cost of time away from normal activitiesPatient Health Questionnaire-9 (PHQ-9) [64, 65]Generalised Anxiety Disorder Questionnaire (GAD-7) [66]Global study-specific patient satisfaction/improvement score (Visual Analogue Scale: VAS) and whether they would recommend each treatment experienced to other patientsPotentially modifiable cognitive and behavioural psychological variables shown to predict onset and perpetuation of other functional bowel symptoms: negative perfectionism [67], avoidant and ‘all or nothing’ behaviour subscales of the Behavioural Response to Illness Questionnaire [68] (CC-BRQ), and the Brief Illness Perception Questionnaire (BIPQ (CC)) [69]

A copy of trial outcome measures is available from the trial manager on request.

### Participant timeline

The study flow chart is shown in Fig. 2.

#### Study visits

##### Visit 0: prescreening: eligibility assessment

Patients referred from primary care or identified in secondary or tertiary care clinics will be approached by a suitably trained and delegated local researcher who will screen for basic eligibility by telephone or face-to-face interview (based on patient choice) on the basis of a simplified inclusion/exclusion criteria proforma (i.e. self-reported constipation for more than 6 months, difficulty passing stool and/or infrequent passing of stool, at least two medications tried for relief of symptoms). Patients will be recorded on a screening log and each will be allocated a sequential trial screening number. Patients will be provided with adequate explanation of the aims, methods, anticipated benefits and risks of the relevant interventions and will take away or be posted an invitation letter and a Patient Information Sheet. Patients will be given at least 24 h to consider participation and invited to attend clinic for a more detailed discussion with a suitably trained researcher. The simplified criteria will be used in marketing and promotional materials and will be made available on the study websites with the Participant Information Sheet for patients to self-screen. Those responding to marketing and promotion of the study will be prescreened by the national coordinating centre and referred to their nearest participating trust.

##### Visit 1: screening, consent and baseline assessments

Visit 1 will be conducted face-to-face in clinic. Following a detailed discussion about the trial, eligible and agreeable patients will complete written informed consent. Screening and confirmation of eligibility will be followed by standardised medical and surgical history by interview including previous medication usage. Clinical examination findings (carried forward if performed previously within last 3 months) and standardised examination of the perineum/anus/rectum/vagina will be performed.

Baseline assessments include several key validated assessments that profile patients for important characteristics informing disease pathophysiology and important potential predictors of treatment response. This includes the constipation and irritable bowel syndrome modules of the Rome III questionnaire [70], the Cleveland Clinic Constipation Score Questionnaire [71], brief chronic pain, autonomic symptoms [72] and joint hypermobility [73] assessments and St. Mark’s Faecal Incontinence Score [74]. All were selected on the basis of trade-off between adequate detail and brevity. These instruments have been collated into a single booklet with design and presentation optimised by patient representatives. Participants will complete the questionnaire booklet (containing baseline, primary and secondary outcomes listed above), and be given a baseline 2-week patient diary and journal. All participants will be asked to complete the 2-week patient diary prior to INVEST, HT or HTBF interventions and prior to stopping laxatives.

Urinary pregnancy testing will be made available to women of child-bearing potential at eligibility assessment and advice will be given to all women regarding the need to prevent pregnancy during the study intervention period. Randomisation to HT-, HTBF- or INVEST-guided intervention will be completed at the end of visit 1.

##### Visits 2–5: interventions

Participants randomised to treatment without INVEST will undergo four sessions of standardised therapy (HT or HTBF) (Tables 1 and 2). Those randomised to INVEST will have additional radio-physiological investigations (Table 3) prior to being stratified to receive either HT or HTBF. A review of all related AEs and changes in confounding medications will be conducted at each intervention visit.

##### Visits 6–8: follow-up outcome assessments (3, 6 and 12 months)

The standardised outcome questionnaires booklet will be completed and the 2-week Bowel Diary and Patient Journal completed and returned, including a review of all related AEs and changes in confounding medications. In order to maximise completeness of data collected, the 3- and 6-month follow-up visits will be conducted face to face wherever possible. Follow-up at 12 months can, however, be conducted by telephone. The 6-month time point at which the primary outcome is recorded will coincide with the end of a protocol-imposed ‘quarantine’ period during which a participant’s response to therapy will remain unconfounded by treatment progression.

### Sample size for the trial

The sample size has been calculated using the primary clinical outcome change in PAC-QOL score. A 0.4-point (10% of scale) reduction in PAC-QOL score [75–77] with a variance estimate conservatively set at a standard deviation (SD) = 1 will be considered clinically relevant.

To detect a mean change of 0.4 in PAC-QOL score (SD = 1) with 90% power and 5% significance level, 132 per arm or 264 participants in total will be required for the comparison of HT and HTBF (No-INVEST arm).

For the secondary comparison of INVEST versus No-INVEST a reduction of 0.4 points (SD = 1) will also be considered clinically meaningful. To detect an effect size of 0.4 with 90% power and at 5% significance level requires 90 participants in the INVEST arm assuming 264 participants have been recruited to the No-INVEST arm.

Allowing for a 10% loss to follow-up, a sample size of 147 is needed in the HT and HTBF arms and 100 in the INVEST arm. A total sample size of 394 patients across the three arms is required.

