**Methods/design:**

A three-arm, parallel-group, multicentre randomised controlled trial.

Objectives: to determine whether standardised specialist-led habit training plus pelvic floor retraining using computerised biofeedback is more clinically effective than standardised specialist-led habit training alone; to determine whether outcomes are improved by stratification based on prior investigation of anorectal and colonic pathophysiology. Primary outcome measure is response to treatment, defined as a 0.4-point (10% of scale) or greater reduction in Patient Assessment of Constipation–Quality of Life (PAC-QOL) score 6 months after the end of treatment. Other outcomes up to 12 months include symptoms, quality of life, health economics, psychological health and qualitative experience.

Hypotheses: (1) habit training (HT) with computer-assisted direct visual biofeedback (HTBF) results in an average reduction in PAC-QOL score of 0.4 points at 6 months compared to HT alone in unselected adults with CC, (2) stratification to either HT or HTBF informed by pathophysiological investigation (INVEST) results in an average 0.4-point reduction in PAC-QOL score at 6 months compared with treatment not directed by investigations (No-INVEST).

Inclusion: chronic constipation in adults (aged 18–70 years) defined by self-reported symptom duration of more than 6 months; failure of previous laxatives or prokinetics and diet and lifestyle modifications. Consenting participants (*n* = 394) will be randomised to one of three arms in an allocation ratio of 3:3:2: [1] habit training, [2] habit training and biofeedback or [3] investigation-led allocation to one of these arms. Analysis will be on an intention-to-treat basis.

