## Methods/design

### Primary objectives

To determine whether standardised specialist-led HT plus pelvic floor retraining using computer-assisted direct visual biofeedback (HTBF) is more clinically effective than standardised specialist-led habit training alone (HT)To determine whether outcomes of such specialist-led interventions are improved by stratification to HTBF or HT based on prior knowledge of anorectal and colonic pathophysiology using standardised radio-physiological investigations (INVEST)

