### Trial design

The study design is a three-arm, parallel-group, multicentre RCT. The trial provides two comparisons: HT (group 1) compared with HTBF (group 2); and investigation-led treatment (group 3) compared with management without investigation (groups 1 and 2) (Fig. 2). Based on our knowledge of the characteristics of the population we expect approximately 50% of those in group 3 to be allocated to each of the two treatments to which individuals are randomised in groups 1 and 2.

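### The 0.4-point INVEST effect behind the 90% power does not fit hypothesis 1 and the 50:50 treatment mixes; if the tests act only by steering treatment, the difference is at most 0.2 (about 37% power) unless HTBF is worse than HT in non-FDD patients

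*Protocol article*

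**What the plan says.** The Abstract gives two hypotheses at 6 months. The first is that HTBF improves PAC-QOL by an average of 0.4 points over HT in unselected patients. The second is that treatment stratified by investigation "results in an average 0.4-point reduction in PAC-QOL score at 6 months compared with treatment not directed by investigations".

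Sample size for the trial carries the second figure over: "For the secondary comparison of INVEST versus No-INVEST a reduction of 0.4 points (SD = 1) will also be considered clinically meaningful". On that basis the same section gives the size of the third group: "To detect an effect size of 0.4 with 90% power and at 5% significance level requires 90 participants in the INVEST arm". The pooled comparator for this figure is set at 264.

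Under Trial design, the INVEST comparator is groups 1 and 2 pooled. The Abstract randomises the arms 3:3:2, so that pool is half HT and half HTBF. For the INVEST arm, Trial design says "we expect approximately 50% of those in group 3 to be allocated to each of the two treatments". The Modified Rome III criteria section sends patients with FDD (about 50%) to the group 2 intervention and the rest to the group 1 intervention.

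The standing of the comparison varies. Primary objectives lists it: "To determine whether outcomes of such specialist-led interventions are improved by stratification to HTBF or HT". Sample size for the trial calls it the secondary comparison.

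**The concern.** INVEST adds no new therapy. It redistributes the two therapies that the comparator already receives in about the same proportions. Its advantage can therefore come only from better matching of patients to treatment, unless being tested helps in some other way. With an average HTBF benefit of 0.4 to redistribute, it is not obvious that matching alone can yield a further 0.4.

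The Discussion section says the trial should inform whether costly invasive tests are warranted before specialist management. A reader who takes the 90% power at face value may read a non-significant INVEST result as strong evidence that the tests add nothing. If the attainable difference is about half the planned one, such a result would be likely even with stratification working fully.

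**Working it through.** **Inputs.** From Sample size for the trial: difference 0.4, SD 1, 5% significance (two-sided assumed, which reproduces the stated figures), 90% power, 90 v 264, 10% loss. From the Abstract: average HTBF benefit 0.4 and allocation 3:3:2. From Trial design and Modified Rome III criteria: FDD share p of about 0.5, FDD to HTBF, non-FDD to HT.

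**The plan's own figures.**
- HT v HTBF: 2 × (1.960 + 1.282)² / 0.4² = 131.3, so 132 per arm, as stated.
- INVEST with 264 fixed: 1 / [0.4² / (1.960 + 1.282)² − 1/264] = 87.4, so 88 (89 by t-test). The stated 90 is within two patients.
- SE = √(1/90 + 1/264) = 0.122. Power at 0.4 = Φ(0.4/0.122 − 1.960) = 0.906 (0.905 by t-test).
- Losses: 132/0.9 gives 147 and 90/0.9 gives 100; 2 × 147 + 100 = 394, as stated.

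**What the design implies.** Let a and b be the HTBF-minus-HT benefit in patients classed by the tests as FDD and non-FDD. Measure gains against everyone receiving HT.
- INVEST gain: p·a.
- No-INVEST gain: 0.5[p·a + (1−p)·b].
- Hypothesis 1: p·a + (1−p)·b = 0.4, so p·a = 0.4 − (1−p)·b.
- Difference: 0.4 − (1−p)·b − 0.2 = **0.2 − (1−p)·b**.

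With b = 0 this is 0.2 for every p, so a departure from 50% FDD does not raise the ceiling.

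**At p = 0.5, 90 v 264, SD 1:**

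| b | a | INVEST difference | Power |
|---|---|---|---|
| 0.4 | 0.4 | 0 | none beyond the 5% level |
| 0.2 | 0.6 | 0.10 | 13% |
| 0 | 0.8 | 0.20 | 37% |
| −0.2 | 1.0 | 0.30 | 69% |
| −0.4 | 1.2 | 0.40 | 91% |

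For an average HTBF benefit D other than 0.4, the difference is D/2 − (1−p)·b. With b at or above 0, a difference of 0.4 therefore needs D of at least 0.8, twice hypothesis 1.

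**Sensitivity.**
- If the SD after baseline adjustment were 0.8 (an assumption), power at 0.2 would be Φ(0.25/0.122 − 1.960) = 0.535, about 54%.
- With no losses (100 v 294, SD 1), power at 0.2 is 41%.

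**Precision at SD 1.**
- Difference detectable with 80% power: (1.960 + 0.842) × 0.122 = 0.34.
- 95% CI half-width: 1.960 × 0.122 = 0.24.
- An estimate below 0.40 − 0.24 = 0.16 excludes 0.4. If the true difference is 0, the chance of this is Φ(0.161/0.122) = 0.91.
- If the true difference is 0.2, the CI excludes 0 with probability 0.37 and, by symmetry, excludes 0.4 with probability 0.37. In the remaining quarter or so it contains both.

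**The case against.** The strongest reply is that 0.4 is a target, not a forecast. The sample size section justifies it as clinically meaningful, sizing on the smallest worthwhile difference is standard, and the power at 0.4 is as stated. This stands as far as the calculation goes. It does not cover the Abstract, which states 0.4 as the hypothesised result for both comparisons without noting the tension between them.

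Second, the tests might help other than by steering treatment. Group 1 sessions are tailored to the individual, and Table 1 offers splinting and pelvic floor exercises where appropriate, which proctography findings could inform. Patients know they were investigated and report the outcome themselves. These routes are possible, so 0.2 is not an absolute limit. But hypothesis 2 and the objective attribute the gain to stratification, and the article neither proposes a direct effect nor says that therapists see the detailed results.

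Third, a reader might infer that 0.4 requires biofeedback to harm non-FDD patients. That goes too far: a negative b means only that they do better on HT alone. The Rationale for choice of comparators reports larger or exclusive benefit in some subgroups and describes no such disadvantage in the others.

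Fourth, SD 1 is described as conservative and the model adjusts for baseline. This is fair, but at SD 0.8 power at 0.2 is still only about 54%.

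Finally, a true gain of at most 0.2 is half of what the protocol calls meaningful, so missing it need not be a wrong decision. This also stands. The trial can often exclude 0.4, and cost-effectiveness is assessed separately.

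**Conclusion.** The sample size arithmetic is correct. The fault is that the 0.4 hypothesised for INVEST does not fit hypothesis 1 and the treatment mixes. If the tests act only by steering treatment and the average HTBF benefit is 0.4, the INVEST difference is at most 0.2 unless HTBF is worse than HT in non-FDD patients. Reaching 0.4 would need b = −0.4 at 50% FDD, or an average HTBF benefit of at least 0.8. Power at 0.2 is about 37% at SD 1, against the 90% stated at 0.4.

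Two stronger readings are not supported. One is that the stated power is miscalculated; it reproduces. The other is that a non-significant INVEST result could never show the tests to be of little use. Non-significance alone does not show absence of benefit, but a CI that excludes 0.4 does rule out the gain the protocol calls clinically meaningful.

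The primary versus secondary labelling is a separate, plain inconsistency. It matters here because Primary objectives gives equal standing to the less well supported question.

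**What to change.** In hypothesis 2 and Sample size for the trial:
- Present 0.4 for INVEST as a target (minimum worthwhile) difference rather than the expected result.
- State the assumption that investigation acts only by directing patients to HT or HTBF.
- State that, under hypothesis 1 and without HTBF being worse than HT in non-FDD patients, the largest difference is 0.2, for which 90 v 264 gives about 37% power at SD 1 (80% power at about 0.34).

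State that the INVEST comparison will be interpreted by its 95% CI (half-width about 0.24) against both 0 and 0.4. A non-significant result alone will not be taken to show no benefit; a CI excluding 0.4 will be taken to rule out the stated clinically meaningful gain.

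Reconcile the label in Primary objectives with that in Sample size for the trial.

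The cost is a less favourable stated power; no extra patients are needed. Recruiting for 90% power at 0.2 in the same ratio would take about 353 v 1,034 analysed participants, so restating the claim is the proportionate remedy.

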### Recruitment

All recruiting sites have been chosen based on feasibility assessments and ability to recruit the required number of participants during the recruitment time frame. An assessment of competing studies, research experience and required resources to conduct the study was also undertaken to ensure that targets can be achieved. The recruitment rates at each site will be monitored throughout the course of the study and barriers to recruitment identified and addressed as they arise. Reserve sites have been identified to address any shortfalls in recruitment. If a larger than anticipated dropout rate occurs, it will be possible to recruit further patients above that suggested in each arm to maintain study power.

### Assignment for interventions

#### Sequence generation and allocation

Randomisation sequence will be computer-generated. Randomisation will take place after consent, eligibility and baseline assessments. We will use a secure, online, access-controlled randomisation system managed by the UKCRC registered, Barts and the London, Pragmatic Clinical Trials Unit (PCTU).

#### Stratification for therapy

As for previous studies in this area we expect to recruit very few men. To ensure balanced randomisation within gender, and secondarily within centres, randomisation will be stratified by gender and then women by centre.

#### Allocation concealment mechanism

The randomisation system is user-access-controlled to maintain allocation concealment from blinded individuals.

#### Blinding

Patients and clinicians are necessarily aware of both INVEST and treatment allocations after randomisation. The primary outcome and several other outcomes are self-reported. All those involved in developing the statistical analysis plan will be blinded to allocation status until the plan is signed off, and no analyses of outcomes will be undertaken until that is done. To minimise observer bias, a blinded researcher will collect outcome data. If a blinded researcher is unavailable, the primary outcome questionnaire will be completed by the participant without assistance and secured in an envelope.

Statisticians performing the analysis will remain blinded.

## Data collection, management and analysis

### Data collection

Data collection methods consist of a mixture of routine clinical data collected by investigators and patient-reported outcomes. Validated questionnaires have been chosen for the majority of the primary and secondary outcome measures, with the exception of the Patient Bowel Diary and Health Utilisation Journal. All participants will be trained in completing the questionnaires at baseline, prior to randomisation and will be provided with a standardised guideline for completing questionnaires to minimise errors or missing data. When available, a blinded outcome assessor will check to verify and confirm questionnaire completion. In order to minimise missing data, follow-up visits up to 6 months post treatment will be conducted face to face. Thereafter, data can be collected over the telephone or via mail). All data will be collected on intention-to-treat principles regardless of protocol excursions and deviations or withdrawal from trial treatments. At least three attempts via two different methods (e.g. telephone and letter), will be made by research staff to make contact and collect follow-up data, after which the participant may be considered lost to follow-up. Participants may be lost to follow-up in the following circumstances:After at least three failed attempts by research staff to make contact via two different methods (e.g. telephone and letter)Participant does not wish to participate in follow-up data collectionDeath or significant incapacity making follow-up data collection impossible

A copy of all Data Collection Forms is available from the trial manager on request

### Data management

Each recruiting site will be required to keep accurate and verifiable source notes in the medical record relevant to each study participant’s inclusion and continued participation in the study.

Data will be collected, transferred and stored in accordance with Good Clinical Practice (GCP) guidelines and data protection requirements. The PCTU SOPs and study data management plan and SOP will define the exact process of data collection, transfer, storage and quality control of study data.

A secure online trial database will be provided by the PCTU to enable remote data entry at sites where this is feasible. This database will provide built-in data validation range checks. Additional quality control will be performed by the central study team on the study data prior to review by the DMC and statistician. These checks will consist of:Repeating data entry (into a separate data table/database provided by the data manager) for a random sample, 10% of the baseline and final outcome data and comparing it with the main database. Discrepancies will be checked against the Case Report Form (CRF) to ensure data entry errors on validation are not counted and only those errors that occurred within the main database will be counted. These errors will be cleaned and correctedValues for each variable will be sorted by the statistician, and those at the extremes will be checked to ensure that they are either correct or within the expected range

Error rates of 1% for primary outcomes and 3% for the remaining data will need to be achieved. The error rate (*r*) will be calculated by comparing the number of errors (*e*) with the total number of CRF fields (*t*): *r* (%) = (*e*/*t*) × 100. If the prespecified error rates are not achieved, data checking and cleaning will be repeated (in additional random 10% lots) and continue until the error rate is met. Missing data will be handled according to the statistical analysis plan. In addition on-site monitoring will enable source document verification of records and will follow the PCTU trial monitoring SOPs and the trial monitoring plan.

All patient-identifiable data, such as Consent Forms, screening and identification logs will be stored in the investigator site files in secure, locked cabinets and offices, accessible only to delegated members of the study team. Secure methods of data transfer will be used to return CRFs to the coordinating site for centralised data entry, monitoring, quality control and in compliance with GCP. A copy of the CRF is held at the site in accordance with GCP.

